#### Follow-up evaluations

The restorations will be evaluated after 1 week by the operator, and after 1 and 2 years by two independent evaluators (Table 
1). Follow-up is planned and funded for 2 years; it may be extended to 5 years (as recommended for indirect dental restorations by the FDI) if the grant can be extended.

**Table 1 T1:** Schedule of enrollment, interventions and assessments

	**Study period**				
	**Enrollment**	**Allocation**	**Postallocation**		**Closeout**
Time point	- ≤ 1yr	0	1 wk	1 yr	2 yr
**Enrollment:**					
Eligibility screen	X				
Informed consent	X				
Allocation		X			
**Interventions:**					
(composite or ceramic inlay/onlay)		X			
**Assessments:**					
Baseline variables					
(inlay/onlay, premolar/molar, vital/non vital, operator, sex, date of birth, restoration volume etc.)	X	X			
Outcome variables					
FDI criteria			X	X	X
Radiograph	X		X	X	X
Impression			X	X	X

#### Data collection

Investigators will use a CRF (available at http://cecoia.fr) to record all items required for outcomes analysis. The CRF comprises two adverse events forms (one concerning general health and one concerning inlay/onlay-related events). Patient data will be anonymous because patients will be identified by their inclusion number (the first letter of their first and last name and date of birth only will be registered in the CRF). A clinical research assistant (RB) will visit each center every 20 inclusions to monitor the collection of data (by checking that no CRF field is incomplete) and assess the quality (by comparing the data in the medical record, entered through the online inclusion and randomization software RandoWeb (Assistance Publique – Hôpitaux de Paris (AP-HP), Paris; http://randoweb.aphp.fr), written in the CRF). The data will be entered twice in the database by operators and checked by a data manager (more information about data management procedures is available at http://cecoia.fr: extra and protocole initial sections). Some elements in the CRF allow for checking for operators’ adherence to the protocol.

### Sample size

We estimated the required sample size for the primary outcome (score between 1 and 5, 5 corresponding to the worst score) for the 18 items for each patient. Since the resulting score is an ordinal variable, we used Zhao’s formula, which is based on the expected distribution of responses in each of the five possible ratings
[39]. To the best of our knowledge, no data on the FDI score are available. Consequently, we derived assumptions from previous studies
[25,26,40-47] that involved the USPHS score
[29], with dimensions close to that of the FDI score
[28]. Thus, we derived assumptions regarding the expected distribution of ratings for the ceramic and composite groups for each of the three dimensions (biological, functional and esthetic). As a proxy for the FDI score, the worst score across the three dimensions, we estimated the three sample sizes required to guarantee a power of 80%, with a type I error rate of 1.7% (Bonferroni adjustment for three dimensions), to detect expected differences in distribution of ratings between the ceramic and composite groups for each dimension. We considered the largest required sample size, which was found for the biological dimension. Consequently, with an overall type I error risk of 5%, a sample size of 211 patients would guarantee 80% power to detect a difference between an expected 3% for scores 3, 4 or 5 in one group and an expected 7% in the other group. Finally, since several centers and several operators will participate, we expected that outcomes from a same center and a same operator will be more similar than those from different centers or different operators. We took this intracenter/operator correlation of data and applied an inflation factor
[48,49], which resulted in an estimated sample size of 358 patients. We will include 400 patients to account for patients lost to follow-up, although we will try to avoid missing data on outcome measures (in particular, by compensating each patient with 100 euros (€100) after 2 years)
[50].

The enrolment capacity was estimated to be 75 patients per year for each hospital and 50 patients per year for each private practice. A 1-year period was planned for including these 400 patients.

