#### Primary outcome analysis

The main analysis will compare the final values of the FDI score (worst score over the three dimensions) between the ceramic and composite groups. The main analysis will be adjusted on the following pre-specified variables: inlay/onlay, premolar/molar, vital/non-vital tooth and operator
[53,55]. An ordinal logistic regression model will be used. The operator variable will be modeled as a random effect. The main analysis will take into account missing outcome data by multiple imputation, with the assumption that data are missing at random. We will report the unadjusted analysis as well; that is, the contingency table showing the distribution of FDI scores in the ceramic and composite groups. The distribution of FDI scores will be compared by Fisher’s exact test. All *P* values will be two-tailed, with significance level 0.05.

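### The 80% power quoted for 211 patients does not belong to the 3% versus 7% contrast in scores 3 to 5; it can arise only from a larger, unstated shift between scores 1 and 2

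*Protocol article*

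**What the plan says.** The Sample size section treats the FDI score as ordinal: "we used Zhao’s formula, which is based on the expected distribution of responses in each of the five possible ratings". Because no FDI data were available, the authors derived assumed rating distributions for each of the three dimensions from earlier studies that used another score. For each dimension they sized the trial "with a type I error rate of 1.7% (Bonferroni adjustment for three dimensions") and took the largest result, which came from the biological dimension.

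The conclusion, given for an overall alpha of 5%, reads: "a sample size of 211 patients would guarantee 80% power to detect a difference between an expected 3% for scores 3, 4 or 5". The rate set against this is "an expected 7% in the other group". This contrast is the only effect size given for the trial.

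The 211 is then inflated to 358 for correlation within centres and operators, and to 400 for losses. Since 400 is the whole trial, 211 is also a total. The shares assumed for scores 1 and 2 do not appear. Under Primary outcome analysis, P "values will be two-tailed, with significance level 0.05".

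**The concern.** A gap of 4 points between two small percentages normally takes far more than about 105 patients per arm to detect with 80% power, so the sentence looks wrong on sight.

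What is at stake is how the result will be read. On this scale 1 is a perfect restoration and 5 is one that needs replacement, so scores of 3 or worse are the part that readers will care about most. Told that the trial was all but certain to have 80% power for 3% versus 7%, a reader would take a null result as good evidence against a difference of that size. If the power really comes from the boundary between scores 1 and 2, a null result says little about scores 3 to 5.

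**Working it through.** **Inputs from the article:** 3% and 7% with scores 3 to 5; 80% power; alpha 1.7% (0.05/3) per dimension and 5% overall; two-sided tests; 1:1 allocation; totals of 211, 358 and 400.
**Assumed here, because the article does not give them:** the shares of scores 1 and 2 in each arm.

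**1. The contrast as printed, with two proportions.** Per arm, n = (z₁₋α/₂ + z₀.₈)² × [p₁(1−p₁) + p₂(1−p₂)] / (p₂−p₁)². The variance term is 0.03×0.97 + 0.07×0.93 = 0.0942.
- Alpha 1.7%: (2.387 + 0.842)² × 0.0942 / 0.04² = 614 per arm, 1,227 in total.
- Alpha 5%: (1.960 + 0.842)² × 0.0942 / 0.04² = 462 per arm, 924 in total.

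Other standard variants (one-sided, pooled variance, continuity correction) give totals from 734 to 1,340. None comes near 211.

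**2. Power for 3% versus 7%.** Power = Φ(0.04 / √(0.0942/n) − z₁₋α/₂), with n per arm and independent patients.

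| Total N | Alpha 1.7% | Alpha 5% |
|---|---|---|
| 211 | 15% | 27% |
| 358 | 26% | 41% |
| 400 | 29% | 45% |
| 422 (211 read as per arm) | 31% | 47% |

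**3. Zhao's formula on the same two categories.** N = (z₁₋α/₂ + z₀.₈)² × (1 − Σ((p_c+q_c)/2)³) / (3θ²) for equal arms. Here θ is the probability that a patient in one arm scores better than a patient in the other, plus half the probability of a tie, minus 0.5. For 97/3 against 93/7, θ = 0.02 and Σ = 0.95³ + 0.05³ = 0.8575. At 1.7%, N = 10.42 × 0.1425 / 0.0012 = 1,238; at 5% it is 932. The choice of formula therefore does not explain 211.

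**4. Can the formula return 211 with an added shift between scores 1 and 2?** Yes. Under proportional odds, 3% versus 7% fixes the odds ratio at (0.07/0.93)/(0.03/0.97) = 2.43. With 60% scoring 1 in the better arm, the other arm has 38.1%, so the distributions over score 1, score 2 and scores 3 to 5 are 60/37/3 and 38.1/54.9/7. Then θ = 0.1141 and Σ = 0.2152. At alpha 0.05/3, N = 10.47 × 0.7848 / (3 × 0.01301) = 210.5, which rounds up to 211.

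**5. How large must that shift be?** Solving for N = 211 at alpha 1.7% over assumed score-1 shares in the 3% arm:
- 3% arm has more perfect scores: gaps of 13.5 points (share 97%), 15.0 (95%), 17.6 (90%), 20.4 (80%), 21.6 (70%), 21.8 (60%), 21.1 (50%), 17.5 (30%) and 14.3 (20%).
- 3% arm has fewer perfect scores: gaps of about 20 to 26 points, for shares from 70% down to 20%.

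Dividing scores 3 to 5 differently moves these gaps by about 0.3 points.

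**6. How the clustering step bears on this.** The inflation factor is 358/211 = 1.70. On the article's own reasoning, 358 clustered patients are worth 211 independent ones. Power for 3% versus 7% at 5% is then 27%. The 41% applies only if the 358 are fully independent.

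**The case against.** The strongest reply is that the article never sized the trial on a two-category test. It names an ordinal formula, it speaks of differences in the distribution of ratings, and the planned analysis is ordinal logistic regression. The 3% and 7% can be taken as shorthand for the assumed distributions. Under proportional odds, with about 55 to 60% perfect scores in the better arm, the formula gives 211 to 212 at alpha 0.05/3. The gap between scores 1 and 2 would then be implied by the model and not be a separate effect. The full distributions may also stand in the original protocol, which the article says can be obtained from the trial website.

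Much of this stands. It gives 211 a credible origin, and leaving input tables to a fuller document is no fault in an article. It does not make the printed sentence true. The match depends on an unstated score-1 share: the same odds ratio needs 267 patients at 80% perfect scores and 778 at 95%. Even where 211 is reached, the power comes mainly from a shift of about 22 points between scores 1 and 2, while the sentence credits it to scores 3 to 5.

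Three stronger readings are tempting, and the documents do not support them:
- **That 211 is an arithmetic error.** The distributions behind it are not shown, and plausible ones reproduce it.
- **That the added gap must be 18 to 22 points.** This fits only part of the range of assumed shares in step 5.
- **That, with equal score-1 shares, the formula always needs more than 12,000 patients.** It gives 1,238 at a shared 0%, 2,606 at 5%, 7,735 at 20%, and reaches 12,376 only at 30%.

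**Conclusion.** The point holds as a misattributed effect size. As printed, the power claim is out by a factor of about 5.8 in sample size at alpha 1.7% (1,227/211) and about 4.4 at 5% (924/211). Reading 211 as per arm does not rescue it, nor does using all 400 patients.

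The two-proportion figures rest only on inputs in the article. The range of 13 to 26 points rests on assumed score-1 shares of 20 to 97% in the 3% arm when the shift runs in its favour, and 20 to 70% when it runs against it. The 27% relies on the article's clustering inflation being right; the 41% treats 358 patients as independent.

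A reader might infer that the trial is too small for its ordinal primary analysis. That does not follow: power for that analysis depends on the whole distribution, which the article does not show.

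**What to change.** Rewrite the power statement in the Sample size section:
1. Give the five-category distributions assumed for the biological dimension in both arms, which produced 211.
2. Say that the 80% refers to that whole-distribution shift at the 1.7% level.
3. Remove the assurance of 80% power for 3% versus 7%.
4. State that, for 3% versus 7% in scores of 3 or worse taken alone, power at two-sided 5% is about 27% if the clustering inflation holds (358 worth 211 independent patients) and at most about 41% with 358 independent patients.

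The cost is rewording one paragraph. Enrolment stays at 400, and the design and primary analysis do not change. The only downside is a less favourable stated figure.

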### Randomization sequence generation

From a literature review, we considered four major factors that could differentially influence the performance of ceramic and composite inlays and onlays (inlay/onlay, premolar/molar, vital/non-vital tooth and operator), and that we should aim for balanced distribution of these factors between the two groups. Consequently, treatment allocation will involve minimization with a 30% random element. Minimization was preferred over stratified randomization from the results of extensive simulations showing minimization with the lowest predictability and imbalance between treatment groups, considering the trial’s sample size and these four factors (details about these simulations and the results are available at http://cecoia.fr)
[51,52].

### Allocation concealment

The operator will obtain each randomization allocation through a centralized secured web-based interface that runs the minimization algorithm (RandoWeb). The sequence is thus concealed until the intervention is assigned.

### Implementation

The minimization algorithm was added to the RandoWeb software. It was programmed by an independent statistician. Investigators will enroll participants (inclusion numbers are obtained by use of RandoWeb).

### Blinding/masking

Operators cannot be blinded to the randomization because the intervention differs between both arms (in particular, surface treatments of the upper and intaglio surfaces of the restoration). Moreover, a dentist can easily recognize each material, so neither operators nor evaluators can be blinded. Patients are not blinded, firstly because a few patients had been asked if they would prefer one material to the other and most did not have any preference; secondly because it would complicate the clinical session because the block is inscripted with the name of the material and the intervention differs between both arms; and thirdly because another dentist could tell them if their restoration is made of composite or ceramic.

Therefore, the trial will be open-label. Randomization was thus planned as late as possible to insure that the tooth cavity would be prepared in the same way for both groups and to limit bias due to the absence of blinding. Interventions were standardized as much as possible (in particular, similar adhesive luting procedure) to enhance similarity. The statistician will be blinded to the treatment arms during data analysis.

### Statistical methods

The data will be analyzed by an independent statistician. The unit of analysis will be the patient (only one tooth treated per patient). The demographic and clinical characteristics of patients and treated teeth will be described for both treatment arms with the usual statistics: mean and SD or median and interquartile ranges for quantitative variables, number of subjects, and percentages for qualitative variables
[53]. The analyses will be performed according to the intention-to-treat principle
[54].

#### Primary outcome analysis

The main analysis will compare the final values of the FDI score (worst score over the three dimensions) between the ceramic and composite groups. The main analysis will be adjusted on the following pre-specified variables: inlay/onlay, premolar/molar, vital/non-vital tooth and operator
[53,55]. An ordinal logistic regression model will be used. The operator variable will be modeled as a random effect. The main analysis will take into account missing outcome data by multiple imputation, with the assumption that data are missing at random. We will report the unadjusted analysis as well; that is, the contingency table showing the distribution of FDI scores in the ceramic and composite groups. The distribution of FDI scores will be compared by Fisher’s exact test. All *P* values will be two-tailed, with significance level 0.05.

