#### Interpretation

Only two randomized studies were identified, which compared ceramic and composite materials for inlay or onlay manufacturing. In 2005, a study compared 80 VITA Mark II (ceramic; Vita Zahnfabrik, Bad Säckingen, Germany) and Paradigm (composite; 3M Espe, St Paul, MN, USA) CAD/CAM inlays in 43 adults after 3 years with use of the US Public Health Service (USPHS) modified criteria
[29]. The composite inlays performed better for only two items: color match and restoration fracture
[25]. In 2006, a study compared 58 CEREC, Vita Dur N (two ceramics; Vita Zahnfabrik), Brilliant DI (Coltene/Whaledent AG, Altstätten, Switzerland) and Estilux (two composites; Heraeus Kulzer GmbH, Hanau, Germany) inlays in 37 patients after 10 years with use of the California Dental Association criteria
[30]: survival was similar for all inlays when repairs were not considered failures (75 to 80%) and was better for CEREC ceramic inlays than other inlays when repairs were considered failures (80% versus 51 to 67%)
[26]. Data on the material to use for manufacturing inlays or onlays are thus controversial and a RCT is needed.

The main objective of the CEramic and COmposite Inlays Assessment (CECOIA) randomized controlled trial (RCT) is to compare the clinical efficacy of composite and ceramic inlays or onlays for treating moderate substance loss of posterior teeth in adults according to recent consensus outcomes. Secondary objectives include the overall quality, wear and survival of inlays and onlays made of both materials, and prognostic factors of restoration failure, including patient-related items.

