### Outcomes

#### Primary outcome

The primary outcome, clinical efficacy of materials, will be measured by use of the Fédération Dentaire Internationale (FDI) World Dental Federation instrument for assessing dental restorations, described in 2007
[28] and updated in 2010
[38]. This instrument contains three dimensions (18 items): biological (six items), functional (seven items) and esthetic (five items). Each item is assessed by clinical examination on a 5-point Likert scale (1 corresponding to a perfect restoration and 5 corresponding to a restoration that needs to be replaced), and collected in the CRF. All items but one are assessed by the dentist; the remaining item is patient-reported satisfaction. The primary outcome is the worst score for all items (ranging from 1 to 5) at 2-year follow-up (the best material will be the one with the lowest score).

Operators and evaluators, who will assign scores, will be trained in the FDI criteria by means of the e-calib web-based  software (http://zep01793.dent.med.uni-muenchen.de/moodle/) and group training sessions. They will use the evaluation kit specifically designed for evaluating the FDI criteria (EX-KIT 150/250, Deppeler, Rolle, Switzerland).

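### The missing-at-random imputation of 2-year FDI scores has no exception for restorations replaced or lost through failure before the visit, although their outcome is known

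*Protocol article*

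**What the plan says.** All references are to the protocol article.

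- **Primary outcome:** "The primary outcome is the worst score for all items (ranging from 1 to 5) at 2-year follow-up". The ends of each item's scale are given as "1 corresponding to a perfect restoration and 5 corresponding to a restoration that needs to be replaced".
- **Follow-up evaluations:** "The restorations will be evaluated after 1 week by the operator, and after 1 and 2 years by two independent evaluators". No other scoring visit is scheduled.
- **Statistical methods:** "The analyses will be performed according to the intention-to-treat principle".
- **Primary outcome analysis:** "The main analysis will compare the final values of the FDI score (worst score over the three dimensions"). On absent values: "The main analysis will take into account missing outcome data by multiple imputation, with the assumption that data are missing at random".
- **Data collection:** "The CRF comprises two adverse events forms (one concerning general health and one concerning inlay/onlay-related events"). No section links these forms to the FDI score or to the imputation.
- **Secondary outcomes:** survival is to be evaluated only if follow-up is extended beyond the funded 2 years, although the Abstract lists it among the secondary outcomes without that condition.

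No section says which score a restoration receives if it was replaced or lost before the 2-year visit.

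**The concern.** The article is not silent on missing outcomes. It gives one rule for all of them. That rule is reasonable for a patient who moves away or misses the visit. It does not suit a patient whose trial restoration fractured at 18 months and was replaced. There is then nothing to score at 2 years, the reason is the outcome itself, and the correct category is known.

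Imputation under missing at random would draw a value for that patient from patients with similar recorded data whose restorations could still be examined. A known failure could then enter the analysis as a good score.

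The Background describes ceramics as brittle and more likely to fracture than composites, so early failure may plausibly differ between the arms. With survival analysis deferred, no other analysis described for the funded 2 years is sure to pick up these failures.

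**Working it through.** **1. What happens to an early failure if the text is followed literally**

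| Step | Source | Consequence |
|---|---|---|
| Outcome is the score at 2 years | Primary outcome | A restoration no longer in the mouth cannot be examined |
| Scoring at 1 week, 1 year and 2 years only | Follow-up evaluations | A failure between visits has no scheduled score of its own |
| Score 5 = needs replacement | Primary outcome | The failure belongs to a category of the scale |
| Intention to treat | Statistical methods | Patient stays in the allocated arm; no score is assigned |
| Missing outcomes imputed under missing at random, no exception | Primary outcome analysis | The only rule the text offers for an absent score |

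**2. Inputs for an illustration of size**

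The article gives no early failure rate, so it has no figure of its own to reproduce on this point. The nearest figures are in the Sample size section: 3% and 7% with scores 3, 4 or 5 on the biological dimension, and 400 patients allocated 1:1, that is 200 per arm. At those rates the expected numbers are 200 × 0.03 = 6 and 200 × 0.07 = 14.

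Assumptions that are not in the documents:

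- A share *f* of the score 3 to 5 results are early failures treated as missing.
- They are imputed from the remaining patients of the same arm.
- Nothing in the imputation model predicts the failure.

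**3. Formula**

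With true rate *p*, the rate after imputation is q = p(1 − f) / (1 − p·f).

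**4. Same share in both arms**

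For f = 50%:

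- Arm at 3%: 0.015 / 0.985 = 1.52%
- Arm at 7%: 0.035 / 0.965 = 3.63%
- Difference: 2.1 points, against 7 − 3 = 4.0 points if failures are scored 5

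| f | Rates after imputation | Difference |
|---|---|---|
| 0 | 3.0% vs 7.0% | 4.0 points |
| 25% | 2.3% vs 5.3% | 3.1 points |
| 50% | 1.5% vs 3.6% | 2.1 points |
| 75% | 0.8% vs 1.8% | 1.1 points |

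**5. Odds ratio**

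The odds after imputation are p(1 − f)/(1 − p). With the same *f* in both arms the factor (1 − f) cancels, so the odds ratio stays at (0.07/0.93)/(0.03/0.97) = 2.43.

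If *f* differs between arms, the odds ratio is multiplied by (1 − f₂)/(1 − f₁), where arm 2 is the arm at 7%:

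- Half of the poor results are early failures in arm 2 and none in arm 1: 2.43 × 0.5 = 1.22, rates 3.0% vs 3.6%.
- The reverse: 2.43 / 0.5 = 4.87, rates 1.5% vs 7.0%.

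The distortion can therefore go either way. These figures collapse the ordinal score into two groups. The effect on the planned five-category model cannot be computed, because the article does not give the expected distribution over the five scores.

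**The case against.** The strongest reply is that the article never says these patients count as missing. Score 5 can hold them, and intention to treat is compatible with giving it to them. The Sample size section mentions missing outcome data alongside loss to follow-up, so the imputation sentence may be meant for absent patients only. The imputation model is not described and might use the 1-year score or recorded events. A failed restoration still in place at 2 years is scored 5 in any case. A coding rule may also stand in the full protocol or analysis plan, which are not shown.

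Much of this stands, and it makes the point conditional. A reader might infer that early failures have no 2-year score and are erased from the comparison; the documents do not say so. What does not fall away is that the only stated rule, taken as written, covers these cases and gives the wrong answer for them. Neither intention to treat nor the loss-to-follow-up wording assigns them a score. A 1-year score in the model would not reliably help with a restoration that was sound at 1 year and broke afterwards.

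Three further inferences are tempting and unsupported:

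- **Repairs.** A reader might think that repaired restorations are mishandled too. They are still present at 2 years and have a score, so imputation does not touch them. Scoring them as they stand fits the stated outcome, and a worst-ever score would need FDI scoring at repair visits, which is not scheduled.
- **Earlier trial.** In the Interpretation section, "survival was similar for all inlays when repairs were not considered failures (75 to 80%) and was better for CEREC ceramic inlays" goes on to say that the advantage appeared when repairs counted as failures. That compares one ceramic with three other inlay types, one of them also ceramic, over 10 years. It does not show that the ranking of ceramic against composite turned on the counting rule.
- **Large loss of power.** Simulated losses at early failure rates of 10% or 15% in one arm rest on rates found nowhere in the article. Setting all other scores equal between the arms makes the difference after imputation zero by construction.

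**Conclusion.** The concern holds in conditional form. The stated missing-data rule has no exception for restorations whose absence at 2 years is itself the failure being measured. If it is applied to them, failures are understated in whichever arm they occur, and the comparison is distorted when early failure differs by material.

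The size is unknown. In the illustration, which borrows the 3% and 7% planning rates and assumes that half of the poor results are early failures with no useful predictor in the imputation model, the difference falls from 4.0 to about 2.1 points.

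A reader might infer that the result must be biased toward no difference or toward the wrong material. That is not general: the odds ratio, which is the scale of the planned ordinal model, is unchanged in this two-group illustration when early failures form the same share of poor results in both arms. It moves down or up when the shares differ.

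**What to change.** Make two linked changes, in the Primary outcome and Primary outcome analysis sections:

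1. Assign score 5 to any trial restoration replaced, lost or removed with its tooth for a restoration-related reason before the 2-year visit, identified from the inlay/onlay-related event form.
2. Restrict multiple imputation under missing at random to patients with no known restoration failure.

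Repaired restorations keep the score they receive at 2 years.

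The cost is about one paragraph. The downside is that the cause of each replacement or loss must be classified, preferably from the records by someone not told the arm. The fields of the event form are not shown in the article, so it should be checked that they capture the replacement or loss, its date and its cause. Because the trial is open-label, the rule should be fixed before outcome data are examined.

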#### Secondary outcomes

Secondary outcomes will include each item of the FDI instrument, patient-relevant outcomes, quantified wear analysis (through silicone impressions) and overall quality of the restoration (as assessed by dentists). Survival may be evaluated if the follow-up is extended.

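### No rule scores a restoration that fails before 2 years; if it falls under the missing-at-random imputation as written, a known failure is imputed from restorations still in place

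*Protocol article*

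**What the plan says.** All references are to the protocol article.

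- **Primary outcome.** "The primary outcome is the worst score for all items (ranging from 1 to 5) at 2-year follow-up". Items are scored by clinical examination on a five-point scale, with "5 corresponding to a restoration that needs to be replaced".
- **Follow-up evaluations.** "The restorations will be evaluated after 1 week by the operator, and after 1 and 2 years by two independent evaluators".
- **Statistical methods.** "The analyses will be performed according to the intention-to-treat principle".
- **Primary outcome analysis.** The final FDI values are compared between arms. For absent scores: "The main analysis will take into account missing outcome data by multiple imputation, with the assumption that data are missing at random". No exception is given and the variables in the imputation model are not listed.
- **Secondary outcomes analysis.** The three dimensions are analysed in the same way.
- **Secondary outcomes.** "Survival may be evaluated if the follow-up is extended". The abstract lists survival among the secondary outcomes, but this section makes it conditional.
- **Data collection.** The case report form has two adverse event forms, "one concerning inlay/onlay-related events". Nothing links that form to the primary score.

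No sentence says how a trial restoration that was replaced or lost, or whose tooth was extracted, before 2 years enters the primary score.

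**The concern.** Once the trial restoration is gone, there is nothing to examine at 2 years. The only rule in the article for an absent outcome is imputation under missing at random. Applied to these patients, it replaces a known bad result with a draw based on restorations that survived. The score is absent because the restoration failed, so the missing-at-random assumption does not suit this group. The failure is also the event that the top of the scale is meant to capture.

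The primary comparison and the three dimension analyses are both exposed. Within the funded 2 years no other planned outcome is sure to pick these failures up, because survival depends on an extension. Operators and evaluators are not blinded, so the way failures count should be fixed before outcome data are seen.

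**Working it through.** **Plan's own figure.** The article gives no figure on early failures, so there is none to reproduce on this point. The sample size of 211 cannot be checked, because the ordinal formula needs the full distribution over the five ratings and that is not printed. Nothing below depends on it.

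**Inputs**

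- *p*, the true share scoring 3 to 5 with early failures included: 3% and 7%. The Sample size section gives these for the biological dimension. They stand in here for the worst score over all 18 items, for which no distribution is given.
- *s*, the share of those cases gone before the 2-year visit: assumed.
- *f* = *p* × *s*, the share of the whole arm gone before the visit.
- 200 patients per arm (400 at 1:1).
- Imputation within arm, without post-baseline predictors: assumed.

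**Formula.** The observed part of an arm is 1 − *f*, and *p* − *f* of it scores 3 to 5. Imputing from the observed part leaves the expected rate at that level:

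analysed rate = (*p* − *f*)/(1 − *f*) = *p*(1 − *s*)/(1 − *ps*)

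**Same share *s* of the poor scores gone in each arm**

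| *s* | 3% arm | 7% arm | Difference (points) |
|---|---|---|---|
| 0 | 3.0% | 7.0% | 4.0 |
| 0.25 | 0.0225/0.9925 = 2.3% | 0.0525/0.9825 = 5.3% | 3.1 |
| 0.50 | 0.015/0.985 = 1.5% | 0.035/0.965 = 3.6% | 2.1 |
| 0.75 | 0.0075/0.9775 = 0.8% | 0.0175/0.9475 = 1.8% | 1.1 |

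Differences are taken before rounding. At *s* = 0.50, 3 patients in one arm and 7 in the other (200 × 1.5% and 200 × 3.5%) would be imputed. About 98.5% and 96.4% of their draws would be a 1 or a 2.

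**Direction, with *f* set separately in each arm**

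| *f* in 3% arm / 7% arm | Analysed rates | Difference (points) |
|---|---|---|
| 0% / 2% | 3.0% vs 0.05/0.98 = 5.1% | 2.1 |
| 1% / 3% | 0.02/0.99 = 2.0% vs 0.04/0.97 = 4.1% | 2.1 |
| 3% / 7% | 0% vs 0% | 0 |
| 3% / 3% | 0% vs 0.04/0.97 = 4.1% | 4.1 |
| 2% / 0% | 0.01/0.98 = 1.0% vs 7.0% | 6.0 |

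The difference shrinks when the arm with more poor scores also loses more restorations early. It hardly moves when both arms lose the same percentage of patients. It grows when early losses sit in the otherwise better arm.

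**The case against.** The strongest objection is that the article never classes a failed restoration as missing. The imputation sentence covers missing outcome data only. The scale's definition of 5, read with the intention-to-treat commitment, allows the opposite reading, in which a restoration already replaced counts as 5. The article is also condensed, and the full protocol or an analysis plan may settle the matter.

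Much of this stands. A reader might infer that the plan sets out to turn failures into successes; the documents do not say so. They do not exclude it either. Intention to treat fixes the arm in which a patient is analysed and does not supply a value that was never measured. The anchor for 5 describes a restoration that is there to be judged. The imputation rule is explicit and carries no exception, so an intended exception should be written beside it.

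Three further inferences are tempting and not supported:

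- *That 93% to 97% of imputed scores would be 1 or 2 on the plan's own figures.* Those figures belong to the biological dimension. The worst score over all items cannot have a lower rate of 3 to 5.
- *That the bias always runs towards no difference.* The second table shows otherwise. The Background describes ceramic as more prone to fracture and composite as less wear-resistant, so early failures and poor late scores could fall in different arms.
- *That a definite loss of power follows.* This would need failure rates, a split of scores 1 and 2, and an imputation model. The article gives none of them.

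Lastly, the 1-week and 1-year scores could enter the imputation model and weaken the effect. That helps only in part: a failure before 1 year has no 1-year score, and a sudden fracture can follow a good one.

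**Conclusion.** The point holds conditionally. The primary score is tied to an examination at 2 years, missing-at-random imputation is stated without exception, and no sentence gives 5 to an earlier failure. Followed literally, the rule would impute known failures from surviving restorations, for which it is unsuitable.

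The size is illustrative only. If half of the cases scoring 3 to 5 are gone before the visit, the assumed 4.0-point difference becomes about 2.1 points. This rests on the biological-dimension rates standing in for the primary score, on the assumed share gone, and on within-arm imputation without post-baseline predictors. The bias is towards no difference if the worse material also fails early more often, about nil if early failures are equal in the two arms, and can run the other way.

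**What to change.** Add to the Primary outcome analysis section, in substance:

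- A trial restoration known to have been replaced or lost, or whose tooth was extracted for a restoration-related reason, before the 2-year visit is scored 5 in the primary analysis. In the dimension analyses, the dimension responsible for the failure is scored 5.
- Multiple imputation under missing at random, with the 1-week and 1-year FDI scores among the predictors, is used only for patients whose restoration status at 2 years is unknown.

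The text should also name the handling of an extraction judged unrelated to the restoration, since that status is known but is not a failure of the material.

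The cost is a sentence or two, plus a coded judgement, made without knowledge of the arm, on the cause of an extraction and the responsible dimension. A form for restoration-related events already exists. Its fields are not shown, so the sponsor should confirm that it records replacement, loss and extraction with their dates and causes.
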